### Study design

We will use a retrospective cohort study design using longitudinal data to evaluate the effects of prescribing apixaban versus warfarin and then versus other DOACs for prevention of stroke and SE in AF on key effectiveness and safety outcomes using non-interventional primary care data.

### Setting/data sources

Patient data used in this study will be obtained from several sources: primary care data on UK National Health Service (NHS) patients from Clinical Practice Research Datalink (CPRD) Gold and Aurum databases, additional data on hospital events and mortality on UK NHS patients with linked data from the Hospital Episodes Statistics (HES) and Office for National Statistics (ONS) databases, and results from the ARISTOTLE trial.

#### ARISTOTLE

ARISTOTLE was a randomised, double-blind trial completed in 2011, comparing apixaban with warfarin in the prevention of stroke and SE. The trial included 18 201 patients with AF and at least one additional risk factor for stroke. The trial was designed to test for non-inferiority of apixaban compared with warfarin, and showed apixaban superiority for (1) the primary outcome of stroke or SE (HR 0.79, 95% CI 0.66 to 0.95),^7^ (2) the safety endpoint of major bleeding (HR 0.69, 95% CI 0.60 to 0.80), and (3) death from any cause (HR 0.89, 95% CI 0.80 to 0.99). The ARISTOTLE findings led to the National Institute for Health and Care Excellence (NICE) guidelines on stroke prophylaxis in patients with AF recommending apixaban as a treatment. Baseline patient characteristics from ARISTOTLE will be used in selection of participants in Objective 1.

#### CPRD Gold

CPRD Gold is a database containing anonymised data from over 625 primary care practices across the UK (approximately 13 million patient records) and is representative of the UK population with respect to age, gender and ethnicity.^11^ Gold contains information on clinical diagnoses, prescribing, referrals, tests and demographic/lifestyle factors. General practices must meet prespecified standards for research-quality data to contribute data.

#### CPRD Aurum

CPRD Aurum contains primary care records similar to Gold but based on practices using EMIS software, whereas Gold has data from practices using Vision software. CPRD Aurum contains data on 19 million patients from 738 practices (10% of English practices) with 7 million active patients.^12^

### Selection of participants

Participants will be selected from CPRD Gold and Aurum between 1 January 2013 and 31 July 2019. All patients will need to have been registered with a practice contributing research quality data for at least 6 months. Participant selection criteria will then vary by objective as detailed below.

#### Objective 1

An overview of each of the steps for participant selection for Objective 1 is provided in figure 2.

**Figure 2 F2:**
[figure not shown]
Flow chart illustrating the assembly of a matched trial-analogous cohort of EHR patients. AF, atrial fibrillation; CPRD, Clinical Practice Research Datalink; EHR, electronic health record.

##### Step 1

We will select all (HES and ONS linked) patients in the EHR cohort (CPRD Gold and Aurum) who would have met the following *inclusion* criteria for the ARISTOTLE study, at least 6 months after patient registration in the database on or prior to the index date:

Diagnosis of AF.Age 18+ years.One or more stroke risk factors (age 75 years or older; prior stroke, transient ischaemic attack or SE; congestive heart failure; diabetes mellitus; hypertension).

In ARISTOTLE, patients randomised to apixaban were new users of apixaban while both treatment arms were allowed to be previous users of warfarin, with patients stratified by prior warfarin/VKA exposure. To mirror ARISTOTLE, we will assess trial criteria for apixaban patients on the date of their first prescription of apixaban while allowing patients prescribed warfarin to become eligible at any warfarin prescription date during the study period; furthermore, we will match ARISTOTLE in the proportion of new versus prevalent users in both treatment arms. We will then exclude patients who meet any of the following ARISTOTLE study *exclusion* criteria prior to their eligible-for-inclusion date:

AF due to reversible causes.Mitral stenosis.Increased bleeding risk.Conditions other than AF requiring chronic anticoagulation.Persistent, uncontrolled hypertension.Active infective endocarditis.Current treatment with aspirin >165 mg/day.Simultaneous current treatment with both aspirin and a thienopyridine.Conditions likely to interfere with participation in the trial or cause death within 1 year.Recent alcohol or drug abuse, or psychosocial reasons making study participation impractical.Recent ischaemic stroke (within 7 days).Severe renal insufficiency.Alanine aminotransferase or aspartate aminotransferase >2× upper limit of normal (ULN) or total bilirubin ≥1.5× ULN.Platelet count ≤100 x10^9^/LHaemoglobin <90 g/L.Pregnancy or breast feeding.

Feasibility counts in Gold found approximately 60% of patients with AF prescribed apixaban met the ARISTOTLE trial criteria. Details of the algorithms used in applying the trial criteria to the EHR data are given in the online supplemental file.

10.1136/bmjopen-2020-042947.supp1Supplementary data

##### Step 2

We will select a subset of apixaban patients from our EHR pool to create a cohort that matches the ARISTOTLE apixaban participants on a selection of the following baseline characteristics:

Age.Sex.Body mass index (BMI).Systolic blood pressure (SBP).Congestive heart failure or left ventricular systolic dysfunction.Hypertension requiring treatment.Diabetes mellitus.Prior stroke/thromboembolism.Smoking status.Alcohol consumption.Level of renal impairment.Prior VKA/warfarin exposure.Labile INR in prior users of warfarin.Concomitant use of: aspirin, antiplatelet or non-steroidal anti-inflammatory drug, lipid-lowering drug therapy, or CYP3A4 inhibitor.

This step will generate a group of ARISTOTLE-analogous apixaban patients, with similar baseline characteristics to ARISTOTLE subjects at the point of randomisation (n~9000).

The variables selected are expected to influence the likelihood of the outcomes of interest. Exact selection of matching variables will depend on the quality and completeness of the data available and a balance will be struck between matched sample size and balance. Different methods to facilitate selection of a matched cohort will be explored, such as propensity score matching (PSM) and coarsened exact matching (CEM),^13^ a non-parametric method that may give estimates with lower variance and bias for a given sample size compared than other methods.^14^

##### Step 3

The resulting trial matched sample of EHR apixaban patients will be matched to the warfarin ARISTOTLE-eligible EHR patients (figure 2) using a matching method such as PSM or CEM (final method selected based on giving optimal sample size vs balance). Risk set sampling will be employed in order to ensure similar duration of prior VKA/warfarin exposure for the prevalent users in the apixaban and warfarin EHR cohorts. The covariates for consideration in matching between EHR treatment arms or construction of a propensity score (PS) model will include the variables listed in step 2 along with additional EHR variables such as data source (Gold or Aurum), socioeconomic status and comorbidities. Each apixaban patient from the ARISTOTLE-eligible EHR patients will be matched 1:1 with the warfarin EHR patient with the closest match giving a trial-analogous cohort of ~18 000.

##### Step 4

The absolute rates and HR for the outcomes of interest (time to: stroke/SE, MI, major bleeding and mortality) will then be calculated. For the primary outcome (time to stroke/SE) the EHR results will be validated against the ARISTOTLE trial results using the criteria detailed in the Statistical Analysis section (Validation of observational results against ARISTOTLE data).

#### Objective 2

We will select patient groups who would not have been included in ARISTOTLE (and therefore would not have been included in the Objective 1 cohort) or who are under-represented in ARISTOTLE. Specifically, this will include patient groups such as patients with an AF diagnosis in the EHR cohort meeting these additional criteria:

Severe comorbid condition: disease with a likelihood of causing death within 1 year or reasons making participation unpractical (such as dementia).

When matching the apixaban and warfarin patients within the patient groups for this objective, additional baseline variables will be considered compared with the list specified for Objective 1, Step 2; namely the H, A, and B components of the HAS-BLED score (Hypertension, Abnormal renal/liver function, Stroke, Bleeding history or predisposition, Labile INR, Elderly (>65 years), Drugs/alcohol concomitantly) not included for Objective 1 matching due to being ARISTOTLE exclusion criteria. In these special patient populations the same outcomes as Objective 1 will be assessed, with absolute and relative rates calculated separately in each special patient group.

#### Objective 3

We will select all patients with AF who have a prescription for apixaban, warfarin, rivaroxaban or dabigatran in the treatment period (between 1 January 2013 and 31 July 2019). The ARISTOTLE trial criteria will be applied, followed by matching the warfarin, rivaroxaban and dabigatran ARISTOTLE-eligible EHR patients in turn to the trial-eligible EHR apixaban patients following the methodology outlined in Objective 1, Step 3. This process will result in the creation of three trial-eligible EHR cohorts: warfarin users matched to apixaban users, rivaroxaban users matched to apixaban users and dabigatran users matched to apixaban users. Matched cohorts of excluded patient groups will also be constructed to enable pairwise comparisons of treatment effects in these groups using the method outlined in Objective 2. In all cohorts, the same outcomes as Objective 1 will be assessed with both absolute and relative treatment effects compared.

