## Introduction

### Background and rationale

Atrial fibrillation (AF) is a common cause of cardiac arrhythmia with symptoms including palpitations, fainting and shortness of breath; however, some patients may be asymptomatic. The prevalence of AF in the UK is estimated to be around 3%,^1^ increasing from 0.2% in people aged 45–54 years to 8.0% in those 75 and older.^2^ The lack of organised atrial contraction in AF can lead to the formation of thrombi, meaning that patients with AF have a fivefold higher risk of stroke which is an important cause of morbidity and mortality.^3–5^

Current UK guidelines recommend use of prophylactic treatment with anticoagulation medication to reduce the risk of stroke. Warfarin, a vitamin K antagonist (VKA) and the previous standard anticoagulant treatment, has many treatment and dietary interactions requiring frequent monitoring of a patient’s international normalised ratio (INR), to maintain anticoagulant activity within a narrow range (2.0–3.0). Low levels put the patient at a higher risk of stroke while high levels lead to a higher risk of bleeding.^6^ In 2011, the first direct-acting oral anticoagulant (DOAC) dabigatran was approved for the treatment of AF in the European Union (EU); it was anticipated to provide easier to manage long-term anticoagulation therapy for patients with AF given the complex safety profile of warfarin. ARISTOTLE, a pivotal randomised controlled trial (RCT) of the DOAC apixaban, demonstrated superiority over warfarin for both prevention of stroke and safety (major bleeding) among individuals with AF.^7^

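### Prior DOAC use is neither excluded, named for matching nor modelled, so patients switched from another DOAC can enter as first-time apixaban users; this can bias the validation HR and, above all, the Objective 3 comparisons

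*Protocol article*

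**What the plan says.** All references are to the protocol article.

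- **Entry rules (Selection of participants, Objective 1, Step 1).** For the apixaban arm, "we will assess trial criteria for apixaban patients on the date of their first prescription of apixaban"; for the warfarin arm the rule is "allowing patients prescribed warfarin to become eligible at any warfarin prescription date during the study period". These rules are meant to reproduce ARISTOTLE, in which "both treatment arms were allowed to be previous users of warfarin, with patients stratified by prior warfarin/VKA exposure". The article adds that "we will match ARISTOTLE in the proportion of new versus prevalent users in both treatment arms". None of the 16 listed exclusions concerns earlier DOAC use.
- **Matching to the trial (Step 2).** The anticoagulant-history variables are prior VKA/warfarin exposure and, in prior warfarin users, labile INR.
- **Matching between EHR arms (Step 3).** "Risk set sampling will be employed in order to ensure similar duration of prior VKA/warfarin exposure for the prevalent users" in the two cohorts. Further covariates are given by example (data source, socioeconomic status, comorbidities); prior DOAC use is not among them.
- **Model (Statistical analysis, Methods of analysis).** The Cox model has treatment group and a two-level term for prior warfarin/VKA status.
- **Objective 3.** Everyone with AF and a prescription of any of the four drugs in the period is selected, the trial criteria are applied, and Step 3 is reused for "matching the warfarin, rivaroxaban and dabigatran ARISTOTLE-eligible EHR patients in turn to the trial-eligible EHR apixaban patients". No index-date rule is stated for rivaroxaban or dabigatran users.
- **Timing.** "In 2011, the first direct-acting oral anticoagulant (DOAC) dabigatran was approved for the treatment of AF" in the EU (Background and rationale); ARISTOTLE was completed in the same year (Setting/data sources).

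**The concern.** Objective 1 tests whether the EHR methods recover the trial result, so the EHR arms should hold the kind of patient the trial compared. The protocol describes trial patients by prior warfarin use alone. The 2013-2019 records also contain dabigatran and rivaroxaban users, on whom Objective 3 depends, and the section on missing prescription data itself mentions patients switching treatments.

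Someone who left another DOAC, possibly after a bleed or another event, or who tolerated it and survived, may differ in risk from a true starter. If so, the validation HR moves for a reason unrelated to whether the matching method works. That HR decides whether the methods go forward to Objectives 2 and 3.

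In Objective 3 the problem is sharper, because the comparator drug may itself be the earlier treatment of some apixaban patients. Nothing stated prevents apixaban starters from being compared with established rivaroxaban or dabigatran users, or one person from contributing to both sides.

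**Working it through.** **1. Following the stated rules for each kind of patient**

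- Dabigatran or rivaroxaban to apixaban, no warfarin history: enters at the first apixaban prescription and is classed VKA-naive.
- Same switch with earlier warfarin: enters at the same point and is classed VKA-experienced; the DOAC period does not count.
- DOAC to warfarin: can enter the warfarin arm at any warfarin prescription in the period.

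At none of the four places where anticoagulant history is handled (Step 1, Step 2, Step 3, Cox model) do the stated variables separate these patients from those with no DOAC history.

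**2. Feasibility count (Sample size, Objective 1)**

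- Aurum: 23 526 × 0.60 = 14 115.6, which reproduces the stated 14 115.
- Gold plus Aurum: 8400 + 14 115.6 = 22 515.6, consistent with the stated figure of more than 22 000.

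**3. Possible shift in the HR**

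Inputs from the document: trial HR 0.79; EU-subgroup HR 0.92; validation window 0.69 to 0.99 (Validation of observational results against ARISTOTLE data).

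Assumptions, not in the document: share of apixaban patients with prior DOAC use, f = 5-30%; their stroke/SE hazard relative to other apixaban patients, after matching, r = 0.7-2.0. Switchers are placed in the apixaban arm only.

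Observed HR ≈ true HR × (1 − f + f × r)

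True HR 0.79:
- Lowest: f = 30%, r = 0.7: 0.79 × 0.91 = 0.72
- f = 10%, r = 1.5: 0.79 × 1.05 = 0.83
- f = 20%, r = 1.5: 0.79 × 1.10 = 0.87
- Highest: f = 30%, r = 2.0: 0.79 × 1.30 = 1.03

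True HR 0.92:
- f = 10%, r = 1.5: 0.92 × 1.05 = 0.97
- f = 20%, r = 1.5: 0.92 × 1.10 = 1.01

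The r at which the observed HR reaches 0.99 is (0.99/HR − 1 + f)/f:

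| f | from 0.79 | from 0.92 |
|---|---|---|
| 5% | 6.06 | 2.52 |
| 10% | 3.53 | 1.76 |
| 20% | 2.27 | 1.38 |
| 30% | 1.84 | 1.25 |

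From 0.79, therefore, only the corner with both a high share and a high hazard exceeds 0.99: at r = 2.0 the share must exceed 0.99/0.79 − 1 = 25.3%. No combination in the range falls below 0.69. If r = 1 there is no shift; if r is below 1 the HR moves down.

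If switchers are also in the warfarin arm, the right-hand side is divided by the same expression for that arm. Equal share and equal relative hazard in both arms would cancel.

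**4. Room for an exclusion**

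- From the stated 22 000: 1 − 15 000/22 000 = 31.8% could be lost before the plan's minimum of 15 000 is breached.
- From the reconstructed 22 515: 1 − 15 000/22 515 = 33.4%.
- If the roughly 4% with missing BMI (Missing baseline data) are not yet netted out: 22 515 × 0.96 = 21 614, and 1 − 15 000/21 614 = 30.6%.

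**The case against.** The strongest reply is that this is a condensed article. It says that "Details of the algorithms used in applying the trial criteria to the EHR data are given in the online supplemental file", the supplement is not shown, and the Step 3 covariates are only examples, so prior DOAC use may be dealt with there. This stands as a limit: nothing can be asserted about the supplement. It does not dispose of the point. The supplement is described as applying the trial criteria, and the article does spell out how anticoagulant history is treated, each time as VKA/warfarin.

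Second, part of what drives a switch is already covered. Prior stroke/thromboembolism and renal impairment are candidate matching variables, comorbidities are added in Step 3, and increased bleeding risk and very recent ischaemic stroke are exclusions. This also stands. The multiplier r must be read as residual risk, so the upper end of the assumed range may be too high.

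Third, a reader might infer that the validation HR is certainly biased, or that every DOAC switcher enters as VKA-naive. Neither is supported. Share and residual risk are not in the document, the direction could go either way, and switchers with earlier warfarin are classed as experienced.

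Fourth, the example that breaches 0.99 at a 20% share starts from 0.92, an EU-subgroup estimate with a 95% CI of 0.56 to 1.52. That is fair; it illustrates sensitivity and is no forecast.

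Finally, for Objective 3 the article does not say that rivaroxaban and dabigatran users enter at any prescription. The supportable point is that no rule is stated.

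**Conclusion.** The concern holds in a limited form. As written, the rules admit patients with earlier DOAC use to both arms and offer no stated means of separating them, which departs from the aim of mirroring ARISTOTLE. That the trial had essentially no such patients is an inference from the 2011 dates and the warfarin-only description; the document does not state it.

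The effect on the validation HR is possible, of unknown size and sign. Under the assumed ranges a true 0.79 stays inside the window except at the extreme corner. A true effect nearer 0.92, which the plan itself treats as plausible for European care, leaves far less margin, and the validation decision could then turn on the switchers. Objective 3 is the more serious exposure, because treatment history there involves the very drugs being compared. The plan should be changed, but nothing here shows that the Objective 1 result would be wrong.

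**What to change.** - **Step 1, both arms:** exclude patients with any DOAC prescription recorded before the index date. For the warfarin arm this includes earlier apixaban. Define new and prevalent user accordingly.
- **Objective 3:** index each DOAC patient at the first recorded DOAC prescription, require no earlier DOAC, allow prior VKA use and match on it.
- **Sensitivity analysis:** keep the unrestricted cohort and report the number of prior DOAC users in each arm.
- **Sample size:** update the feasibility count.

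The exclusion uses prescribing records that the study already relies on. Its cost is a smaller pool: the stated figure of more than 22 000 would have to fall by about 32% to go below the 15 000 minimum, or about 31% if the missing-BMI exclusion is still to come off the 22 515. At an assumed 10% or 20% loss, 20 264 or 18 012 of the reconstructed 22 515.6 would remain. The article gives no counts for rivaroxaban or dabigatran, so the loss in those cohorts cannot be assessed and should be counted before the rule is fixed. If it proves too large, matching or stratifying on prior DOAC use is an alternative.

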#### Sensitivity analyses

Primary and secondary effectiveness outcomes will also be analysed using the on-treatment censoring scheme to investigate whether the extent of treatment discontinuation compromises confidence in the effectiveness analyses.

Exclusion of patient time post-treatment discontinuation in the safety and sensitivity analyses might bias results towards a conclusion of no difference^16^ and risks selection bias due to attrition^17^; the set of patients who switch or discontinue treatment will therefore be examined to ascertain whether biases of this nature may have occurred.

Additional analyses may be performed using methods such as inverse probability of censoring weighting (IPW) or a rank-preserving structural failure time model to estimate the treatment effect that would have been observed in the absence of treatment switching. We will explore the impact of time-varying eligibility by using methods such as a modified treatment strategy IPW.^17^

Adherence will be estimated in the EHR cohort to enable comparisons with the trial and investigate the extent to which this may have influenced differences in treatment effect observed. For apixaban, we will calculate the proportion of days covered (PDC) over a patient’s time when on treatment as a measure of adherence. Warfarin dose is poorly recorded in EHR, therefore warfarin adherence will be estimated by looking at adherence to other long-term daily medications as a proxy measure and by looking at INR control by calculating per cent INR TTR as a measure of overall warfarin treatment regime adherence.

We will perform a supplementary analysis in patients deemed adherent (PDC ≥80% matching ARISTOTLE compliance limit) along with an exploratory subgroup analysis by INR TTR. The different nature of the proxy variables used for adherence in the DOACs (PDC) compared with warfarin (INR TTR) means that the adherence estimates may not be comparable; should great differences in adherence be observed between these exposure groups the definitions of adherence used may need to be reassessed.

Apixaban was a newly available drug with a low number of patients having a prescription in the first year it was available^18^; we will therefore perform a sensitivity analysis with the start of the study period shifted forwards a year to January 2014 to investigate the impact of inclusion of early adopters who may differ from later adopters of a new drug.

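### Objective 1 names no matching or adjustment on index calendar date, although apixaban was newly launched and warfarin patients may enter at any prescription from 2013 to 2019

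*Protocol article*

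**What the plan says.** Under Selection of participants the accrual window is fixed: "Participants will be selected from CPRD Gold and Aurum between 1 January 2013 and 31 July 2019". Objective 1, Step 1 then sets two different entry rules. For apixaban, "we will assess trial criteria for apixaban patients on the date of their first prescription of apixaban". For warfarin, the rule is "allowing patients prescribed warfarin to become eligible at any warfarin prescription date during the study period". Nothing in the article ties a warfarin patient's index date to that of the matched apixaban patient.

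Step 3 presents its covariates as candidates: the Step 2 variables "along with additional EHR variables such as data source (Gold or Aurum), socioeconomic status and comorbidities". Neither list names index date or calendar year. Step 3 adds that "Risk set sampling will be employed in order to ensure similar duration of prior VKA/warfarin exposure for the prevalent users" in the two EHR cohorts.

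Under Methods of analysis, the Cox model contains treatment group and prior warfarin/VKA status. The Sensitivity analyses section notes that "Apixaban was a newly available drug with a low number of patients having a prescription in the first year it was available" and therefore repeats the analysis from January 2014. The Plan for addressing confounding recognises possible channelling towards a new drug and relies on the eligibility criteria and baseline matching to deal with it.

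**The concern.** Time zero is set differently in the two arms. First prescriptions of a drug with slow initial uptake tend to fall late in the window, whereas a warfarin patient can be indexed at any point in it. Two patients alike on every listed covariate may therefore be indexed years apart. Any change over those years in stroke care, event coding or background risk that the matched covariates do not capture would then be attributed to treatment.

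The validation rule makes this matter. The stroke/SE HR must lie between 0.69 and 0.99, so the upper edge is only 1% below the null. A modest bias can carry a null result into the window, or a real benefit out of it. Passing the test is what releases the methods for Objectives 2 and 3, and Objective 3 reuses the Step 3 matching.

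**Working it through.** **1. The plan's own figures.** In the Sample size section, 23 526 × 0.60 = 14 115.6 (stated 14 115), and 8 400 + 14 115.6 = 22 515.6 (stated >22 000). Both reproduce. The article gives no figure for index dates by arm, for trends in outcome rates or for the number of eligible warfarin patients in Objective 1. What follows is an illustration on assumed inputs.

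**2. Do the stated safeguards align calendar time?**
- *Risk set sampling.* Its stated aim is similar prior VKA duration. Two patients with two years of prior warfarin can be indexed in 2013 and 2018. Naive users have no prior duration, so they are not covered.
- *January 2014 start.* This truncates both arms at the same point. It does not equalise what remains (step 5).
- *Cox model.* It has no calendar term.

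**3. Assumed index dates.** The window is T = 6 + 212/365.25 = 6.58 years. Apixaban starts are assumed to rise linearly from zero, giving a mean index time of 2T/3 = 4.39 years; the share in year 1 is 1/T² = 2.3%, in keeping with low early uptake. Three patterns are assumed for warfarin:

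| Warfarin index dates | Mean (years) | Gap, apixaban later |
|---|---|---|
| Uniform | T/2 = 3.29 | 1.1 |
| Falling linearly | T/3 = 2.19 | 2.2 |
| 60% in first 3 months, rest uniform | 0.6 × 0.125 + 0.4 × 3.29 = 1.39 | 3.0 |

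**4. Spurious HR when the true HR is 1.** For an assumed yearly fall d, the multiplier is the mean of (1 − d)^(index time) under apixaban divided by the same mean under warfarin. For a rise, 1 + d replaces 1 − d. Results by simulation, one million draws per arm:

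| Gap | Fall 1% | Fall 3% | Fall 5% | Rise 1% | Rise 3% | Rise 5% |
|---|---|---|---|---|---|---|
| 1.1 | 0.989 | 0.967 | 0.944 | 1.011 | 1.032 | 1.054 |
| 2.2 | 0.978 | 0.935 | 0.894 | 1.022 | 1.067 | 1.113 |
| 3.0 | 0.970 | 0.912 | 0.856 | 1.030 | 1.092 | 1.155 |

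The simple form (1 − d)^gap agrees: 0.97¹ = 0.970, 0.97² = 0.941, 0.97³ = 0.913. If both arms have the same index-date distribution, the multiplier is 1.000 for every trend.

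Against the window of 0.69 to 0.99:
- A true HR of 1.00 with a 3% yearly fall appears as 0.91 to 0.97, inside the window.
- A true 0.92 (the EU subgroup estimate quoted in the article) with a 3% rise and a 3.0-year gap appears as 0.92 × 1.092 = 1.00, outside.
- A true 0.79 with a 5% fall and a 3.0-year gap appears as 0.79 × 0.856 = 0.68, also outside.

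**5. After the January 2014 shift.** Mean apixaban index time becomes (2/3)(T³ − 1)/(T² − 1) = 4.48. Uniform warfarin becomes (1 + T)/2 = 3.79, a gap of about 0.7 years. Linearly falling warfarin becomes 1 + (T − 1)/3 = 2.86, a gap of about 1.6 years. The gap shrinks but remains.

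**The case against.** The strongest reply is that this is silence in a condensed article. The Step 3 covariates are offered for consideration and the extras are examples, so the full protocol may include index date. Figure 2 and the supplement are not shown. How the risk sets are formed is not described, and they could be built on calendar date. The warfarin rule does not say that the earliest prescription is used, so several candidate dates per patient may remain open to the matching. Systolic blood pressure, treated hypertension and lipid-lowering therapy are matching candidates and would absorb part of any trend, whereas the illustration applies the whole trend. The article also acknowledges channelling and residual confounding, and plans to explore time-varying eligibility by weighting.

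Much of this stands. A reader might infer that calendar date was deliberately left off a closed list, or that secular trends are shown to be confounded with treatment. The text supports neither: the list is open, and both the gap and the trend are unknown. A reader might also assume that warfarin entries cluster in the early years; no distribution is given. Nor is longer available follow-up for earlier-indexed patients a bias in itself: with proportional hazards and non-informative censoring, it does not bias a Cox HR.

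The reply does not remove the point. The article gives the entry rules, names covariates down to data source, states what risk set sampling is for and lists the Cox terms. Followed as written, those rules make unequal index dates likely, and no named step corrects them.

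**Conclusion.** The concern holds as a gap in the stated confounding control, not as a demonstrated bias. Bias needs two conditions: index dates that still differ after matching, and outcome rates that change over calendar time beyond what the matched covariates explain. The documents quantify neither. With an assumed 3% yearly fall and a gap of about 1 to 3 years, the spurious multiplier is roughly 0.97 to 0.91; across trends of 1% to 5% in either direction it runs from 0.856 to 1.155. The direction follows the trend, so it would be wrong to read this as a bias that necessarily favours apixaban. With an upper limit of 0.99, even the small end of that range can affect whether the validation criterion is met.

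**What to change.** In Step 3, for naive and prevalent users alike, name index date as a matching or propensity score variable (calendar year or a set window), or state that the risk sets are formed on calendar date. Carry the same rule into the Objective 2 and 3 matches that reuse Step 3. Report the distribution of index dates by arm before and after matching, alongside the baseline tables already planned. If the full protocol already does this, a sentence saying so is enough.

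The data are already held. The cost is some loss of matched pairs, which may not be small if the arms sit years apart; it cannot be sized because the article gives no Objective 1 warfarin count. Putting index year in the propensity score, rather than matching on it exactly, limits the loss and fits the article's stated trade-off between sample size and balance.
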